##### REKKEFØLGE 1:

- |             |           |
|-------------|-----------|
| 1. Smør     | 6. Hytte  |
| 2. Dårlig   | 7. Stang  |
| 3. Strand   | 8. Kart   |
| 4. Brev     | 9. Gress  |
| 5. Dronning | 10. Motor |

«Flott, nå kan du si hvilken ord du nettop leste?»

*Gi deltakeren 90 sekunder, rekkefølgen spiller ingen rolle. Skriv ned hvor mange ord deltakeren klarer. Gjenta prosessen, sorter ordene i rekkefølge 2 før du holder dem opp igjen.*

«Flott, da kan du lese opp ordene igjen.»

##### REKKEFØLGE 2:

- |           |             |
|-----------|-------------|
| 1. Kart   | 6. Dårlig   |
| 2. Hytte  | 7. Dronning |
| 3. Smør   | 8. Brev     |
| 4. Strand | 9. Stang    |
| 5. Motor  | 10. Gress   |

«Bra, kan du gjenta ordene du nettop leste?»

*Skriv ned og gjenta prosess for en tredje gang, to sekunders intervall. Sorter kortene i rekkefølge 3.*

REKKEFØLGE 3:

- |             |           |
|-------------|-----------|
| 1. Dronning | 6. Strand |
| 2. Gress    | 7. Smør   |
| 3. Dårlig   | 8. Motor  |
| 4. Hytte    | 9. Kart   |
| 5. Stang    | 10. Brev  |

### 3. ADL

“Oki, supert. Nå skal jeg spørre deg litt om hva du gjør i hverdagen,”

*Still spørsmålene og se om svaret passer i noen av boksene, hvis ikke kan du grave litt for å få et alternativ som passer i boksene. Gå tilbake og bruk ordliste to for gjenkjennelse og gjenkallelse.*

#### 2.2 Gjenkallelse ordlæringstest

“For noen minutter siden ba jeg deg om å lære en liste med 10 ord. Nå vil jeg at du skal huske disse ordene”

“Nå skal jeg gi den masse ord skrevet på kort. Noen av disse ordene har du allerede sett, og noen av ordene er nye. Jeg vil at du skal si “Ja” hvis ordet jeg viser deg er et du har allerede sett før”

*Sorter inn de nye ordene og bruk rekkefølge 4.*

REKKEFØLGE 4:

- |                  |                     |
|------------------|---------------------|
| 1. Kirke         | 11. Dronning |
| 2. Kaffe         | 12. Hytte    |
| 3. Smør   | 13. Tøffel          |
| 4. Dollar        | 14. Stang    |
| 5. Dårlig | 15. Landsby         |
| 6. Strand | 16. Band            |
| 7. Fem           | 17. Kart     |
| 8. Brev   | 18. Hær             |
| 9. Hotel         | 19. Gress    |
| 10. Berg         | 20. Motor    |

### 4. GDS

“Kjempe bra. Nå skal jeg spørre deg litt om humøret ditt og hvordan du føler deg til vanlig. Jeg vil at du skal fylle ut denne listen,”

*Gi deltakeren GDS og la de svare selv, med blyant som de allerede har. Hjelp ved behov.*

### 5. MMSE

“Du er kjempe flink. Går det bra? Trenger du en pause?”

*Gi pause på 5 til 10 minutter hvis de trenger det.*

“Oki, la oss gå videre, nå skal vi teste litt forskjellige kunnskaper,”

*Gi deltaker blyant og viskelær. Utfør og følg instruksene til MMSE på selve testen.*

## **6. SPPB**

“Veldig bra, nå skal vi få litt fysisk aktivitet. La oss nå begynne kartleggingen. Nå vil jeg at du skal prøve å innta ulike stillinger. Jeg vil først beskrive og vise hver stilling for deg. Så vil jeg at du skal prøve å gjøre det samme. Du skal ikke gjøre noe du føler er utrygt eller noe du ikke klarer. Har du noen spørsmål før vi starter?”

*Husk at du skal bruke stoppeklokke. Gjerne si ifra om at det er det du gjør på mobilen din, sånn at de ikke blir fornærmet.*

*1) Begynn med stående stilling, samlede føtter.*

«Nå vil jeg vise deg stillingen» *demonstrer* «Jeg vil at du skal forsøke å stå med føttene samlet, inntil hverandre i ca 10 sekunder. Du kan bruke armene, bøye knærne eller bevege kroppen for å holde balansen, men prøv å ikke flytte på føttene. Prøv å holde stillingen til jeg ber deg stoppe»

*Husk stoppeklokke og scoringsark. Stå ved siden av deltakeren for å hjelpe han/henne inn i stillingen. Gi akkurat nok støtte til deltakerens arm for å unngå at personen mister balansen. Når deltakeren er i stillingen spør du*

«Er du klar?» *Slipp takket og start tidtakingen idet du sier: «Klar, start»*

*Stopp stoppeklokken og si «Stopp» etter 10 sekunder eller hvis deltakeren flytter føttene og forlater stillingen eller griper tak i armen din.*

*Hvis deltakeren ikke klarer å holde stillingen i 10 sekunder noter resultatet og gå videre til ganghastighet, dropp altså de andre stående øvelsene.*

*2) Stående stilling - semi-tandem.*

«Nå skal jeg vise deg den andre stillingen» *demonstrer* «Nå vil jeg at du skal forsøke å stå med ved siden av hælen på den ene foten og inntil stortåen på den andre foten i ca 10 sekunder. Du kan velge hvilken fot du har først, det som er naturlig for deg. Du kan bruke armene, bøye knærne eller bevege kroppen for å holde balansen, men prøv å ikke flytte på føttene. Prøv å holde stillingen helt til jeg ber deg stoppe»

*Stå ved siden av deltageren for å hjelpe han/henne inn i semi-tandem stillingen. Gi akkurat nok støtte til deltagerens arm for å unngå at hun/han ikke mister balansen. Når deltakerens føtter står samlet, spør du:*

«Er du klar?» *Slipp takket og start tidtakingen idet du sier: «Klar, start»*

*Stopp stoppeklokken og si «Stopp» etter 10 sekunder eller hvis deltageren flytter føttene og forlater stillingen eller griper tak i armen din.*

Hvis deltakeren ikke klarer å holde stillingen i 10 sekunder noter resultatet og gå videre til ganghastighet, dropp altså de andre stående øvelsene.

### 3) Stående stilling - tandem

«Nå skal jeg vise deg den tredje stillingen» demonstrer «Nå vil jeg at du skal forsøkte å stå med hælen på den ene foten og inntil tærne på den andre foten i ca 10 sekunder. Du kan velge hvilken fot du har først, det som er naturlig for deg. Du kan bruke armene, bøye knærne eller bevege kroppen for å holde balansen, men prøv å ikke flytte på føttene. Prøv å holde stillingen helt til jeg ber deg stoppe»

Stå ved siden av deltageren for å hjelpe han/henne inn i semi-tandem stillingen. Gi akkurat nok støtte til deltagerens arm for å unngå at hun/han ikke mister balansen. Når deltakerens føtter står samlet, spør du:

«Er du klar?» Slipp takket og start tidtakingen idet du sier: «Klar, start»

Stopp stoppeklokken og si «Stopp» etter 10 sekunder eller hvis deltageren flytter føttene og forlater stillingen eller griper tak i armen din.

[figure not shown]

#### 4m Gangtest

«Nå skal jeg observere hvordan du vanligvis går. Hvis du bruker stokk eller andre ganghjelpemidler og føler du trenger det for å gå en kort distanse kan du bruke det.»

#### A) Første del av ganghastighet

«Denne distansen skal du gå. Jeg vil at du skal gå til den andre enden, i din vanlige hastighet, som om du gikk nedover gaten til butikken.»

Demonstrer øvelsen for deltageren. Bruk oppmarkert rute i rommet. Det er målt til 4 meter.

«Gå hele lengden, over og forbi teip-markeringen før du stopper. Jeg kommer til å gå sammen med deg. Føler du at dette er trygt?»

La deltageren stå med begge føttene inntil startlinjen.

«Når jeg sier du skal starte sier jeg: Klar start.» Når deltageren bekrefter å ha forstått instruksjonen si:

«Klar, Start»

Start tidtakingen idet deltageren begynner å gå. Gå bak og til siden for deltageren. Stopp tidtakingen når en av deltagerens føtter er helt over mållinjen.

#### B) Andre test av ganghastighet

«Nå vil jeg at du skal gjøre det samme en gang til. Husk å gå i din vanlige hastighet, og gå helt over og forbi teip-markeringen.»

La deltageren stå med begge føttene inntil startlinjen.

«Når jeg sier du skal starte sier jeg: Klar start.» Når deltageren bekrefter å ha forstått instruksjonen si:

«Klar, Start»

Start tidtakingen idet deltageren begynner å gå. Gå bak og til siden for deltageren. Stopp tidtakingen når en av deltagerens føtter er helt over mållinjen.

[figure not shown]

*Reise seg test*

### 1) Reise seg fra stol én gang

«Dette er den siste øvelsen. Er det trygt for deg å reise deg opp fra stolen uten å bruke armene? Denne testen måler styrken i beina dine.»

*Demonstrer og forklar øvelsen.* «Først kryss armene over brystet, og sitt slik at føttene er plassert på gulvet: så reiser du deg opp, behold armene i kryss over brystet. Nå vil jeg at du skal prøve å reise deg opp med armene i kryss over brystet.»

*Noter resultatet, stolen er 44 cm høy. Hvis deltakeren ikke klarer å reise seg uten å bruke armene si:*

«Ok, prøv å reise deg med å bruke armene»

*Denne avslutter testen, noter resultatet.*

[figure not shown]

### 2) Reise/ sette seg x5

«Tror du det vil være trygt for deg å reise deg opp fra stolen fem ganger uten å bruke armene?»

*Demonstrer og forklar øvelsen:* «Nå vil jeg at du skal reise deg helt opp, så RASKT du kan fem ganger, uten stopp. Etter at du har reist deg hver gang, sett deg ned og reis deg opp igjen. Behold armene i kryss over brystet. Jeg tar tiden med en stoppeklokke.»

*Når deltakeren sitter på riktig måte, si: «Klar? Reis deg» og start tidtakingen. Tell høyt hver gang deltageren reiser seg, opp til fem ganger. Stopp om deltageren blir sliten eller tungpustet av å reise seg fra stolen flere ganger. Stopp stoppeklokka når han/hun har reist seg helt opp den femte gangen.*

*Stopp også hvis deltakeren bruker armene, etter 1 minutt ikke har fullført 5 repetisjoner. Hvis du er bekymret for deltakerens sikkerhet.*

*Hvis deltakeren er sliten og stopper før fem repetisjoner spør du: «Kan du fortsette?» For å bekrefte dette. Hvis deltageren sier «Ja», forsett tidtakingen. Hvis deltageren sier «Nei,» stopp og nullstill stoppeklokken.*

## 7. STROOP

“Kjempe flott, nå skal du få gjøre noen tester på denne datamaskinen.”

Gi deltakeren pause mens du setter opp datamaskinen og går inn på STROOP programmet, søk i søkefeltet og åpne psychopy filen, dette tar noen minutter, trykk på RUN (grønne knapp og gi data til deltakeren. Forklar ekstra, dette er vanskelig å forstå.)

## 8. Finger Tapping Test

“Den testen er veldig vanskelig, meningen man skal gjøre feil, men du var flink. Nå skal du bare trykke på mellomromstasten masse”.

Finn FTT, ved å søke på FTT eventuelt åpne previous experiments i psychopy. Klikk på run og gi til deltakeren.

## **9. PROMS**

“Nå er vi snart ferdig. Du skal nå få en test som skal se litt på musikk evnene dine,”

Søk på internett explorer (finn favoritter og trykk på PROMS linken. Hvis internett ikke er koblet til så går du på wifi knappen og trykker på koble til eudoram.

Bruk deltakernummer og ikke det som står på introduksjonssiden for dem. Fyll inn første side for dem som et intervju.

Finn fram test headsettet og la deltakeren ta dem på. Og hjelp dem med å justere lyd og starte testen.

## **10. FMRI**

“Kjempe flott, da er vi ferdig, du har vært en sikkelig helt. Nå skal du snart få gå inn i skanneren hvor vi skal se på hjernen din. Men først skal du få litt pause, trenger du å gå på do? Spise osv?”

Vise dem hvor kantinen og Narvesen er hvis de er sulten, og toalettet er rett nede i gangen. Når dere er klare og det er fMRI tiden deres går dere rett over gangen og bort til skanneren. Derfra følg egen protokoll og introduser deltakeren til radiografene.

**GODT JOBBA!**

## Appendix E fMRI Protokoll

### FMRI protokoll

Muntlige instruksjoner før skanning begynner:

**Nå skal du inn i fMRI maskinen. Det er for at vi skal kunne se hvordan hjernen din ser ut.**

**Det hele tar ca 30 minutter. Har du lyst til å høre på musikk mens du er der inne?**

**Hva slag type musikk liker du?**

**Vi har klassisk, rock, pop, world, folk og jazz musikk.**

**Flott! Det er viktig at du slapper helt av og har øynene lukket. Jeg setter på et bildeshow med naturbilder; men du trenger ikke se på det. Og når vi sier at du må lukke øynene er det veldig viktig at du gjør det.**

(Gi deltakeren og ID nummer til radiografene, de går gjennom sjekklister og låser inn eiendeler osv)

Skru på datamaskinen, eller få radiografene til å hjelpe deg å logge på. Gå inn på datamaskinen - paradigmer (R) - ALMUTH og velg musikk sjanger. Sett på power point presentasjonen og dra den over på den andre skjermen. Pass på at skjermen er på ved å trykke på M2 på den svarte boksen. Sjekk at den hvite boksen har fMRI data knappen på 80 % volum. Og at master volumet er stilt inn på EMO lydnivå. Og pass på at Windows Media Player er på fullt.

**Nå starter opptakene.** (sier radiografene, de tar over snakking fra nå av)

LOC  
Asset cal 33d  
SAG  
DTI

Mens disse går, skriv inn all data for deltaker-nummer, dato, ID, Musikk, Sjanger, fMRI og eventuelle merknader underveis. Husk å skrive hvem som samler inn data også, (altså hvem du er).  
Bruk 1. Side som mal.

Nå er det klart for fMRI. Skriv hvilken som begynte med, musikk eller ikke musikk. Stopp den andre musikken og lysbildene. Skru av skjermen. (svart boks, trykk på M1)

**Hei, nå kommer det to opptak hvor du skal ligge og tenke på det du vil. Her er det veldig viktig at du har øynene lukket. Det ene opptaket du skal høre på musikk, men ikke i det andre.**

Sett på den andre filen i mappen med musikk merket MR også f. Eks jazzsang. Alle sangene er merket med «Sang» på slutten av sjangeren. Sett på musikken når radiografene setter på opptaket. Alle sangene er lengre enn opptaket, så ikke vær bekymret for å gå tom for tid. Husk at annenhver gang skal musikken først og annenhver gang sist. Sjekk hva som ble gjort sist ved å bla i fMRI boken. Når opptaket er ferdig stanser du musikken.

Da var du ferdig. Ta med deltakeren ut og si at de gjorde en god jobb, uavhengig om de gjorde det eller ikke. Deretter følg dem dit de skal nå. Husk du er ansvarlig.

Godt jobba!

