## Secondary Neuroscientific Outcomes

Title: Integrity of fibre tracts

Description: Changes in the integrity of fibre tracts can be measured by Diffusion Tensor Imaging (DTI).

Time frame: Testing before randomisation and after 12 months of intervention.

Test: DTI can be used to look at the loss of fibre rays in the hippocampus, which we assume to be stronger in the other intervention groups compared to the music group. DTI also sees several biomarkers in AS, which correlates with boiler-like functions (Nir et al., 2013).

Title: Plasticity changes in the brain's morphography

Description: Voxel-based Morphography on Structural MRI, it is possible to look at differences in hippocampus, functions in the default mode network (DMN), and how music archives the brain in the default mode network. As well as functional contexts on the groups before and after intervention.

Time frame: Testing before randomisation and after 12 months of intervention.

Test: In early stages of AD, the activity of the posterior part of DMN will begin to degenerate, while in the anterior and ventral networks, activity will increase (Damoiseaux, Prater, Miller, & Greicius, 2012). We want to watch DMN with silence and a choice of various music pieces (selected by participants; see Appendix C), and see if degeneration will slow down with music intervention.

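### Optional background music before the resting-state runs, with no washout specified, leaves participants who accept it without a music-free silence run

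*Protocol*

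**What the plan says.** Appendix E (fMRI Protokoll) is a step-by-step operator script.

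- Before scanning, the participant is asked "Har du lyst til å høre på musikk mens du er der inne" (whether they would like to hear music while inside).
- The operator opens the trial folder, "ALMUTH og velg musikk sjanger" (choosing the genre), and starts the slide presentation. The listed sequences are then localiser, calibration, SAG and DTI.
- When the functional runs are due, the instruction is "Stopp den andre musikken og lysbildene". The screen is switched off and the participant is told "Hei, nå kommer det to opptak hvor du skal ligge og tenke på det du vil" (two recordings are coming, during which they may think of what they like) and "Det ene opptaket du skal høre på musikk, men ikke i det andre" (music in one, none in the other).
- On order: "Husk at annenhver gang skal musikken først og annenhver gang sist" (music first every other time, last every other time). The operator looks in the fMRI log book to see what was done last.
- On ending the music run: "Når opptaket er ferdig stanser du musikken" (stop the music when the recording is finished).

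No length is given for any interval before or between the runs.

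The use of these runs is described under Secondary Neuroscientific Outcomes, in the entry on plasticity changes: "We want to watch DMN with silence and a choice of various music pieces". The time frame is before randomisation and after 12 months, and the aim is to see whether degeneration slows with the music intervention.

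**The concern.** Alternating the run order is a sensible safeguard against carry-over from the music run: in half the sessions the silence run comes first. The safeguard works only if nothing musical precedes the first run. The instruction to stop the other music shows that music can be playing until just before that run, and the script then calls for a separate music file for the run itself. The silence-first order therefore does not give a music-free silence state for anyone who took up the offer.

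Two further features add variation. Exposure before the runs depends on each person's choice. Order follows the last entry in the log book, so it is not tied to the participant. What is at stake is how cleanly the silence condition, and its change over 12 months, can be interpreted in the default mode network outcome.

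**Working it through.** There is no planned figure to reproduce, because the point concerns procedure. The check is the sequence of steps plus simple timing.

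**Inputs**
- Total scanner time: about 30 minutes (Appendix E).
- Scan length: 7.14 minutes (Appendix C, on the music for the scanner), taken as the length of one run and read either as a decimal or as 7 min 14 s.
- Number of runs: two, one with music (Appendix E).
- Order: alternated by log book (Appendix E).
- Interval before or between runs: not stated.

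**Time available for background music**
- Decimal reading: 2 × 7.14 = 14.28 min, and 30 − 14.28 = 15.72 min.
- Minutes-and-seconds reading: 2 × 7.233 = 14.47 min, and 30 − 14.47 = 15.53 min.

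About 15.5 to 15.7 minutes remain for the earlier sequences and any pauses. This is an upper bound on background music, since the 30 minutes is approximate.

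**What precedes the silence run**

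| Background music | Run order | Before the silence run |
|---|---|---|
| Accepted | Silence first | Background music, stopped just before |
| Accepted | Music first | Music run |
| Declined | Silence first | No music |
| Declined | Music first | Music run |

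Let a be the proportion who accept (not given in the protocol) and assume alternation splits sessions equally. The share of sessions in which silence follows music is a + (1 − a)/2 = (1 + a)/2. That is 50% at a = 0, 75% at a = 0.5 and 100% at a = 1. Alternation alone would hold it at 50%.

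**Order across visits**

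Number the sessions as they appear in the log book. If a participant's baseline is session i and the 12-month scan is session j, strict alternation gives the same order at both visits only when j − i is even. Recruitment and scanning are continuous (Project Management and Time Line), so nothing makes that difference even. If its parity is as good as arbitrary, about half of participants change order between visits.

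**Possible dilution (illustration only)**

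Suppose a fraction c of the music effect persists into a silence run that follows music, equally after background music and after the music run. A within-session music-minus-silence difference would then be (1 − c) of its full size for acceptors. For decliners, averaged over the two orders, it would be (1 + 1 − c)/2 = 1 − c/2.
- c = 0.2: 80% for acceptors, 90% for decliners.
- c = 0.5: 50% for acceptors, 75% for decliners.

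The protocol gives no value for c. The calculation shows direction and scale, not an estimate.

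**The case against.** The strongest reply has four parts.

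1. Order is counterbalanced and recorded. The operator logs which run came first and has fields for music, genre and remarks, so order, and probably background music, could be examined in the analysis. This is right as far as it goes. A record lets exposure be described, but it cannot supply a music-free silence run for those who accepted.

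2. The protocol defines no music-minus-silence estimand. It says the network will be observed in both states and frames the question as change over 12 months. This stands: the dilution figures apply only if such a difference is analysed.

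3. The outcome is minor. Statistical Methods treats everything beyond the primary comparison on the two primary outcomes as exploratory, and neither brain age from T1-weighted MRI nor the GDS uses these runs. This stands and limits the weight of the point.

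4. Music during the early sequences may help people with Alzheimer's disease tolerate scanning. SAG is probably the structural scan behind the brain-age outcome, although the script does not say so. Removing music there could put a primary outcome at risk for the sake of an exploratory one. This is a fair reason not to ban background music altogether.

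Three stronger readings are tempting and are not supported. A reader might infer that silence follows music in every session; the music is an offer, and a decliner scanned silence-first has heard none. A reader might infer that there is no gap at all; the script is a checklist without timings, and stopping the music, switching off the screen and speaking to the participant take some unquantified time. A reader might infer bias between arms, for instance because a year of singing lessons makes acceptance at 12 months more likely. The same script applies to all arms, and the protocol shows neither differential acceptance nor carry-over lasting into the run.

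**Conclusion.** The point holds in a limited form. For participants who accept background music, the script yields no silence run free of preceding music in either order, so alternation does not deliver the clean silence condition it appears to offer. For those who decline, the problem is confined to music-first sessions. Depending on acceptance, between 50% and 100% of silence runs follow music, with up to about 15.5 minutes of background music beforehand. Because order is not tied to the participant, it can also change between visits.

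The likely consequence is some dilution of any silence-versus-music comparison and extra noise in within-person change. Its size rests on how long music effects persist, which the protocol does not address. It touches one exploratory secondary imaging outcome and leaves the primary outcomes alone. This is a cheap improvement, not a threat to the trial's main conclusions.

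**What to change.** Amend Appendix E as follows, for both visits:

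- Stop any background music before the DTI, so that an existing scan without music precedes the first run. Music may stay during the localiser and SAG for comfort.
- State a short music-free interval between the two runs, with its length written down.
- Keep each participant's run order and background-music condition the same at baseline and at 12 months. For example, alternate order by participant at baseline and look it up at follow-up.
- Log run order and background music (yes or no) as explicit fields.

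The cost is an edit to the script and the log sheet. Stopping the music before the DTI and fixing the order add no scan time; the interval between runs adds only its own length. Participants have no music during the DTI, which may be slightly less comfortable.

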## **Project Management and Time Line for the Project**

Project start: 1. March 2018

Data retrieval of pre-scanning, pretesting and similar before intervention: 01.02.2018 – 01.06.2018

Recruitment will be continuous until we reach our goal. Recruitment will start in March 2018.

Initiation of intervention will also be continuous and start as each participant is scanned and tested. Scanning and testing will be done from March until June, or longer if necessary.

Intervention period: 01.03.2018 – 01.03.2019

The intervention period may vary for the different participants, but not the length, which will last for 12 months. This means that if a participant joins the project on June 1, 2018, the intervention will begin from that date and last for 12 months from that date.

Analysis of brain imaging data: 01.02.2018 to 01.02.2020

Analysis of imaging data will occur on a continuous basis after each participant has been in the scanner and taken the psychological tests. Since this is to be done twice, it is assumed that much time will go for analysis. Statistical analysis comparing data between interventions will not commence before the end of data collection and preparation (database lock) for all participants.

Article writing and publishing of results: 01.02.2020 to 01.02. 2021

During this period, the project team will work on preparing data for publishing, creating guidelines/manuals for interventions that can be used by the municipality and the rest of the country. The intervention material, such as the music, the music program, the exercise program, will be made available for all who wish to use it, both domestic and internationally.

Recruitment end: 01.01.2020

Recruitment will be an ongoing procedure until we get 135 participants or the project run out of time. Hence the last day of recruitment will be a bit before a year is left of the project so that participants still get the 12 months of intervention and the analysis can be included.

Project end: 01.02.2021

Around the end of the project we wish to send out an evaluation form for participants where we ask if they are still home and whether they have moved into a nursing home. We will also ask if we can contact them two and a half years after intervention (which will be before the project ends) and then again 5 years after end of intervention.

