## Appendix C Music used for the brain scans

Music for the scanner, deltakerne får velge en av følgende sjangere:

1. Klassisk stykke - Praetorius Six Dances from Terpsichore

<https://www.youtube.com/watch?v=kmHR6GWQOWU>

2. Rock – Wild Melodic Metal | Guitar Backing Track Jam

<https://www.youtube.com/watch?v=R0jwsidG4wU>

3. World - PAN FLUTE PERU - INKA TRAIL - CAMINO INCA

<https://www.youtube.com/watch?v=48FZKfcRauM>

4. Jazz –Modern jazz gypsy

<https://www.youtube.com/watch?v=YkrxvqGbqgk>

5. Pop – 80s Pop Funk Backing Track (Dm) | 110 bpm - MegaBackingTracks

<https://www.youtube.com/watch?v=tD8AtHHvzJs>

6. Folk - samme som World

NB: Alle sangene har blitt behandlet i Audacity og endret til 74 decibel (dB) og normalisert for lydvariation. Alle sangene er også blitt kuttet og satt sammen til å vare 8 minutter. Selve skanningen varer 7.14 minutter.

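### Appendix E does not tie a participant's 12-month music/silence order or music piece to the baseline scan, which adds avoidable noise to the change in the secondary default-mode outcome

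*Protocol*

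**What the plan says.** Appendix E (fMRI Protokoll) has two resting recordings, one with music and one without. It tells the operator that music comes first in every second session and last in the others: "Husk at annenhver gang skal musikken først og annenhver gang sist". The operator finds out which is due by looking up the most recent session in the scan book: "Sjekk hva som ble gjort sist ved å bla i fMRI boken". The order used is written down ("Skriv hvilken som begynte med, musikk eller ikke musikk"), together with participant number, date and genre.

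The genre is settled by an oral question just before scanning: "Hva slag type musikk liker du". Appendix C gives the menu ("Music for the scanner, deltakerne får velge en av følgende sjangere"). It lists six genres but five distinct pieces, because Folk uses the same piece as World.

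The recordings serve a secondary outcome. Under Secondary Neuroscientific Outcomes the Protocol says "We want to watch DMN with silence and a choice of various music pieces (selected by participants; see Appendix C"), with the aim of seeing whether degeneration slows. The time frame there is "Testing before randomisation and after 12 months of intervention". The Project Management and Time Line section also treats scanning and testing as a repeated exercise: "Since this is to be done twice".

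No section says that the second scan should repeat the order or the piece of the first.

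**The concern.** The outcome compares each person's scan at 12 months with that person's own baseline. Anything about the session that stays the same drops out of that comparison, and anything that varies goes into the error. Run order could matter here. Under Appendix D the scan follows a long test battery, participants lie with closed eyes, and music may carry over into a silent run that follows it. The piece heard could matter for similar reasons.

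Alternating across sessions balances order on average, but it does not hold order fixed within a person. At stake is precision on one exploratory secondary outcome, with about 40 participants per group expected after attrition.

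**Working it through.** **The plan's own figure.** The Sample Size section gives 40 per group for d = 0.7, two-sided 2.5%, 80% power. The normal approximation gives 39 per group. The exact t-test has power 0.799 at 40. The figure stands, and this point does not touch it.

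**How often the order would switch.** Assume the Appendix E rule is used at both visits, with one shared book for all sessions. Whether a participant's second session falls on a music-first or music-last turn then depends on how many other sessions came between, so the two orders are effectively unrelated. A simulation used these inputs:
- 135 baseline scans spread evenly over 22 months (recruitment from March 2018 to 1 January 2020);
- follow-up at 12 months, give or take half a month (assumed);
- 40 of every 45 participants retained (from the Sample Size section).

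A different order at the two visits occurred in 49.9% of participants on average (95% range 41% to 59%). If the rule were instead read as alternating within each participant, everyone would switch. Neither reading holds the order fixed.

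**Added variance when order is ignored.** Let order shift a music-minus-silence contrast by delta, in SD of the change score with order held fixed. Each visit then carries +delta/2 or −delta/2, with variance delta²/4. With unrelated orders, the change gains

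delta²/4 + delta²/4 = delta²/2.

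The Protocol gives no value for delta, so the range below is an assumption. The power column is only an illustration. It takes 40 per group at the two-sided 5% level set for secondary outcomes, and borrows d = 0.7 from the primary outcomes.

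| Assumed delta | Added variance | Illustrative power |
|---|---|---|
| 0 (order held fixed) | 0 | 0.871 |
| 0.25 | 3.1% | 0.861 |
| 0.3 | 4.5% | – |
| 0.5 | 12.5% | 0.830 |
| 0.8 | 32% | – |
| 1.0 | 50% | 0.714 |

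**Added variance when the logged order is modelled.** In simulations with 40 per arm and unrelated orders, change in order was entered as a covariate. The variance of the arm difference then rose by no more than about 2%, whatever delta was. A constant order effect is therefore largely recoverable. Person-to-person variation in the response to order is not.

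**Piece.** A change of piece would add to these figures. Nothing in the Protocol allows it to be quantified.

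**The case against.** Several points on the other side have force.

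- **Use of the script at 12 months is inferred.** Appendix E is reached from Appendix D, which reads as the baseline session. Appendix D opens with consent and includes the background questionnaire, the physical performance battery and the music-perception test, all scheduled only before randomisation. A reader might take it as fact that half of the participants will switch order. The Protocol does not say so. It gives one scan script, two scan times and no separate rule for the second. Reuse is the natural reading, but it is a reading.
- **The contrast is not defined.** The Protocol does not say that the measure is music minus silence. Under the same additive model, an average of the two runs would carry no order effect.
- **Order is logged and can be modelled.** This is an analysis choice that a statistical analysis plan, not seen here, may already make. The percentages for an analysis that ignores order must not be read as the expected loss.
- **The piece is partly a preference by design.** Participants choose it, and the Protocol does not show that their answers change. Replaying the baseline piece may miss what a participant likes a year later.
- **Alternation is sound counterbalancing.** This is true, but alternating once per participant at baseline keeps the balance across people.

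These objections limit the size and certainty of the point. They do not remove it: a stated acquisition rule leaves order free to vary within a person when it could be held fixed at almost no cost.

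**Conclusion.** The point holds as a minor one. If Appendix E is followed at both visits, about half of participants would have a different run order at 12 months, and the piece may differ too. This adds avoidable noise to the change in the secondary default-mode outcome. The direction is clear if any order or piece effect exists, but the size is unknown. The figure of delta²/2 rests on three assumptions: a music-minus-silence contrast, a value of delta that the Protocol does not supply, and an analysis that ignores the logged order.

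Two stronger readings are not supported. One is that order biases the comparison of arms. The alternation follows the scan book and does not depend on allocation, so it adds noise rather than systematic bias. The 12-month piece is chosen after allocation and could in principle shift with arm, but nothing in the Protocol shows that it would. The other is that the main results are weakened. BrainAGE uses the T1-weighted scans, and depression comes from a questionnaire. Neither primary outcome depends on these runs, nor do the diffusion imaging outcome and the sample size.

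**What to change.** In Appendix E, state that the music/silence order is alternated once per participant, at the baseline scan. At 12 months the operator looks up that participant's own baseline entry in the scan book and repeats the order. Preferably the baseline piece is replayed as well, accepting that it may no longer match the participant's current taste. Where the order at 12 months departs from baseline, include the recorded order as a factor in the fMRI analysis.

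The cost is one or two sentences. Participant number, genre and order are already logged, the balance of order across participants is kept, and no sample size or other outcome changes.
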